## Abstract

**Background:**

Acute-on-chronic liver failure (ACLF) is a common clinical type of liver failure, and patients with acute-on-chronic liver failure are prone to fungal infections, especially the increasing incidence of invasive pulmonary aspergillosis (IPA). Voriconazole is recommended as the first-line antifungal agent in the treatment of invasive aspergillosis; however, no recommendation has been given for patients with severe liver cirrhosis (Child–Pugh C) and liver failure. This trial aims to examine the therapeutic effects and safety of voriconazole in the treatment of IPA in patients with liver failure.

**Methods:**

This study is a non-double-blind randomized controlled trial. The 96 eligible acute-on-chronic liver failure patients complicated with invasive pulmonary aspergillosis will be randomly assigned to receive either the optimized voriconazole regimen or the recommended voriconazole regimen for patients with mild to moderate liver cirrhosis (Child–Pugh A and B), at a 1:1 ratio, with an 8-week follow-up period. The antifungal efficacy of voriconazole will be the primary outcome measure. Plasma voriconazole trough concentration, the laboratory examination (CRP, PCT, ESR, etc.), chest CT, adverse events, and mortality at week 4 and 8 will be the secondary outcome measures.

**Discussion:**

This trial aims to demonstrate the efficacy and safety of voriconazole in the treatment of IPA in patients with liver failure, which is expected to provide a reference for scientific optimization of voriconazole regimens and a realistic basis for the standardized treatment of acute-on-chronic liver failure patients complicated with invasive pulmonary aspergillosis.

**Trial registration:**

The trial was registered with the Chinese Clinical Trial Registry, ChiCTR2100048259. Registered on 5 July 2021.

## Introduction

### Background and rationale {6a}

Acute-on-chronic liver failure (ACLF) is a prevalent kind of liver failure in which patients acquire acute or subacute liver failure as a result of chronic liver disease [1]. Meanwhile, patients with acute-on-chronic liver failure are more susceptible to fungal infections, particularly the rising incidence of invasive pulmonary aspergillosis (IPA), which has been reported to be as high as 5.0–8.3% [2–4], with a significant increase in short-term mortality (73.5–100%) [2, 3, 5].

At present, amphotericin B, voriconazole, and echinocandins are three frequently prescribed drugs for IPA patients. Voriconazole is recommended as the first-line antifungal agent in the treatment of invasive aspergillosis in the guidelines of the Infectious Diseases Society of America in 2016 [6]. The routine intravenous dosing regimen for voriconazole is as follows: 6 mg per kilogram intravenously twice daily on day 1, then 4 mg per kilogram intravenously twice daily for at least 7 days, after which the patient may switch to oral voriconazole at 200 mg twice daily. The loading dose can make plasma trough concentration (*C*_min_) reach the steady-state concentration of voriconazole in the shortest time (24 h), and the final half-life of voriconazole is only 6 h, so it needs to be administered twice a day [7]. Its therapeutic effect and adverse reactions (such as hepatotoxicity, hallucination, mental abnormality, etc.) are closely related to plasma voriconazole trough concentration. Since voriconazole is mainly metabolized by the liver drug enzyme CYP450, liver injury caused by liver cirrhosis and liver failure may decrease the activity or number of metabolic enzymes, resulting in a decrease in voriconazole metabolism and a corresponding increase in the incidence of adverse reactions [7–10]. Voriconazole drug instructions indicate that for patients with mild to moderate liver cirrhosis (Child–Pugh A and B), the loading dose remains unchanged and the maintenance dose is halved. However, there is no recommendation for patients with severe liver cirrhosis (Child–Pugh C) and liver failure.

So far, there are few studies on the use of voriconazole in ACLF patients, and some scholars have analyzed its individualized scheme, but its safety is still unknown. We have retrospectively observed hospitalized ACLF patients complicated with IPA who were treated with voriconazole in our hospital. All of them received the recommended loading dose(400 mg intravenously twice daily on day 1) for Child–Pugh A and B cirrhosis patients, and the maintenance dose was based on the liver damage and their weight. We found that all the four cases’ plasma concentrations exceeded the safe range and then had hallucinations, mental symptoms, and liver toxicity. It can be found that for IPA, the recommended therapy for patients with mild to moderate liver cirrhosis is not suitable for ACLF patients. In addition, due to the slower metabolism in patients with liver failure, the half-life of voriconazole is prolonged and the steady-state time may be different from that of the normal population or patients with mild to moderate liver damage [11]. As a result, not only is it critical to find a more safe and effective administration regimen, but it is also necessary to monitor the plasma concentrations earlier and more closely to determine the best time for plasma concentration monitoring as well as to use voriconazole scientifically to avoid losing the opportunity to use the first-line antifungal agent in the therapy.

### Objectives {7}

Based on the pharmacokinetic profile of voriconazole, the objective of this trial is to examine the efficacy and safety of voriconazole in the treatment of IPA in patients with liver failure, to provide a reference for scientific optimization of voriconazole regimens and a realistic basis for the standardized treatment of patients with ACLF complicated with IPA.

### Trial design {8}

This study is a non-double-blind, randomized controlled, parallel group and non-inferiority trial. A flowchart of the trial is shown in Fig. 1. Participants who meet the eligibility criteria will be randomized respectively into two groups as follows: (1) the experimental group and (2) the control group; they will receive different voriconazole regimens. The protocol reporting follows the Standard Protocol Items for Clinical Trials 2013 (SPIRIT 2013) [12].

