## Interventions

### Explanation for the choice of comparators {6b}

Instruction of voriconazole shows no recommendation for patients with severe liver cirrhosis (Child–Pugh C) and liver failure, so the choice of comparators in this study is based on the recent research on related topics and the previous retrospective studies of our research group [3, 7, 10, 11, 16–18]. The recommended protocol of voriconazole for Child–Pugh A or B liver cirrhosis was chosen as a control to best determine any effects of the interventions.

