### Outcomes {12}

#### Primary outcome

The primary endpoint will be the antifungal efficacy of voriconazole. All patients treated with voriconazole were systematically evaluated by the same investigator on the team. Each patient was evaluated on the basis of case report, imaging (computed tomography scan, CT) findings. CT images of the lung were reviewed by two radiologists. Changes in lesions were assessed visually using computed planimetry to help estimate percentage change. The response categories for complete response, partial response, and treatment failure were the same as those in similar previous studies [16–19]. Complete responses were defined by the resolution of all clinical signs and symptoms and more than 90% of the lesions due to invasive aspergillosis that were visible on radiology. Partial responses were defined by clinical improvement and greater than 50% improvement in findings on radiology. Stable responses were defined by the absence of change from base line or an improvement of less than 50%. Failure of therapy encompassed progression and death due to IPA. Complete and partial responses were classified as successful outcomes.

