### Sample size {14}

We referred to a study about drug monitoring and safety of voriconazole therapy in patients with Child–Pugh B and C cirrhosis; this study suggested that about 30% of patients in group B (loading dose, 200 mg intravenously twice daily on day 1; maintenance dose: 100 mg intravenously twice daily) had voriconazole *C*_min_ > 5 mg/L on the third day of treatment [20].

Based on pharmacokinetic knowledge, we estimate that the rate of patients in the experimental group in this study with *C*_min_ > 5 mg/L after 3 days of treatment with voriconazole will not be lower than that in group B described above. The resulting sample size was calculated as follows:$${N}_{c}={\left({Z}_{1-\alpha /2}\sqrt{\overline{P }\left(1-\overline{P }\right)\left(1+r\right)/r} +{Z}_{1-\upbeta }\sqrt{{P}_{c}\left(1-{P}_{c}\right)+{P}_{T}\left(1-{P}_{\mathrm{T}}\right)/r}\right)}^{2}/{\left({P}_{c}-{P}_{T}\right)}^{2}$$

NC: control group sample size.

PC (control group rate): 0.6, PT (experimental group rate): 0.3,

$$\overline{P }$$ (mean of control group rate and experimental group rate): 0.45.

*r*: grouping ratio, *r* = 1 for 1:1 grouping.

*α*: type I error; *β*: type II error.

Here $$\alpha =0.05, \beta =0.1, Z1-\frac{\alpha }{2}=1.96, Z1-\beta =1.28$$

Substituting into the formula: NC ≈ 42.16. By grouping 1:1, then at least 43 cases were taken from each group. Considering 10% dropout, the study will require recruiting approximately 96 participants for all the groups (*n* = 48 in each group) to adequately test the assumption.

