## Statistical methods

### Statistical methods for primary and secondary outcomes {20a}

In this study, a separate statistical analysis plan will be developed to analyze the data of the treatment group and the control group. The analyses will be based on Consolidated Standards of Reporting Trials guidelines, and all analyses will be on the principle of intention-to-treat, that is, all participants will be analyzed even if some subjects will fail to follow the original plan during the study. This analysis method can better evaluate the effect of the intervention, reduce bias, and be closer to the actual clinical situation. Our researchers are responsible for the follow-up to ensure that relatively complete data are obtained. Subjects who lacked data on the main results will be excluded in the study from the beginning, including missing CYP2C19 gene, lung CT, abdominal ultrasound, G/GM test, Child–Pugh score, and MELD score.

The PASW18.0 statistical software will be used to analyze the data. The counting data will be expressed by rate, and the rate will be compared by the chi-square test. Continuous normal distribution data will be expressed as mean ± standard deviation, *t*-test will be used for comparison between the two groups, non-normal data will be expressed as median (quartile spacing), Mann–Whitney test method will be used for comparison between the two groups, and *χ*^2^ test will be used for counting data. *P* < 0.05 indicates that the difference is statistically significant. The GraphPadPrism5 software will be to draw.

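### The trial is labelled non-inferiority, but no margin is stated and both the sample-size formula and the planned test are for a difference

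*Protocol article*

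**What the plan says.** All references are to the protocol article.

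- **Trial design {8}** states: "This study is a non-double-blind, randomized controlled, parallel group and non-inferiority trial". The term non-inferiority appears nowhere else: not in the abstract, objectives, sample size, statistical methods or discussion.
- **Primary outcome:** "The primary endpoint will be the antifungal efficacy of voriconazole". Complete and partial responses count as success. No expected success rate is given for either arm.
- **Sample size {14}** uses a two-proportion formula with the normal quantile at 1 − α/2 and the squared difference in rates as denominator. Its inputs are "PC (control group rate): 0.6, PT (experimental group rate): 0.3", and these are rates of trough concentration above 5 mg/L, not of antifungal response.
- **Statistical methods {20a}** says that for count data "the rate will be compared by the chi-square test", with P < 0.05 marking a significant difference. It also says that "all analyses will be on the principle of intention-to-treat" and that a separate statistical analysis plan will be written. That plan is not available here.
- **Additional analyses {20b}** plans none.

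**The concern.** A non-inferiority trial asks whether the new regimen is worse than the comparator by no more than a stated amount. That amount, the margin, defines the null hypothesis, enters the sample size and sets the decision rule. Here the label is present and all three are absent.

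A chi-square test has equality as its null hypothesis. If P < 0.05 the arms differ. If P > 0.05 the test has not shown a difference, and this says nothing about how large a deficit remains compatible with the data. In a small trial that deficit can be large.

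The sizing assumes that the experimental regimen halves the share of patients with high trough concentrations (0.6 to 0.3). Loss of antifungal response is then the natural thing for a non-inferiority comparison to exclude, and the discussion says the authors hope the findings may help revise guidelines.

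**Working it through.** **1. The plan's own formula.** Inputs from Sample size {14}: P_C = 0.6, P_T = 0.3, mean 0.45, r = 1, z = 1.96 and 1.28.

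n = [1.96·√(2 × 0.45 × 0.55) + 1.28·√(0.6 × 0.4 + 0.3 × 0.7)]² / (0.6 − 0.3)²
= [1.96·√0.495 + 1.28·√0.45]² / 0.09
= (1.379 + 0.859)² / 0.09 = 55.6.

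The printed result is 42.16, so it does not reproduce. That is a separate fault, as is sizing on trough concentration instead of the primary outcome, and neither adds weight here. What matters for this point is the form of the formula: the denominator is the squared assumed difference and no margin appears. It sizes a two-sided test of difference.

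**2. Numbers per arm.** The plan takes 43 per arm before dropout and recruits 43/0.9 = 47.8, rounded to 48. So 43 is the evaluable number after 10% dropout, and 48 is the number randomised.

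**3. How often the chi-square misses a real deficit.** The response rates are assumptions. Exact enumeration of all outcome pairs, uncorrected chi-square at 0.05:

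| True response, control v experimental | P(non-significant), 43 per arm | P(non-significant), 48 per arm |
|---|---|---|
| 40% v 25% | 67% | 65% |
| 50% v 35% | 70% | 68% |
| 30% v 15% | 60% | 57% |

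**4. Precision.** Half-width of the 95% interval for the difference at a common rate p: 1.96·√(2p(1 − p)/43).

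- p = 0.25: 1.96 × 0.0934 = 18.3 points
- p = 0.40: 1.96 × 0.1057 = 20.7 points
- p = 0.50: 1.96 × 0.1078 = 21.1 points

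**5. Power if a margin were adopted.** Equal true rates p, margin m, non-inferiority declared if the lower 95% limit lies above −m: power = Φ(m/√(2p(1 − p)/43) − 1.96). For example, p = 0.25 and m = 0.20 gives Φ(0.20/0.0934 − 1.96) = Φ(0.18) = 57%.

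| Common response rate | m = 10 points | m = 15 points | m = 20 points |
|---|---|---|---|
| 25% | 19% | 36% | 57% |
| 40% | 15% | 29% | 47% |
| 50% | 15% | 29% | 46% |

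With 48 per arm, power at 20 points is 50-62%. For 90% power at 20 points, assumed common rates of 30-70% require 111-132 per arm before dropout.

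**The case against.** **The analysis plan may settle it.** The article promises a separate statistical analysis plan, and a confidence-interval rule or a per-protocol set would commonly be placed there. Their absence alone is no fault. The margin is different, because it must drive the sample size, and the article prints a complete calculation without one, along with the test and the significance rule. An analysis plan could supply a margin only by overriding those statements, so the contradiction stands.

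**The label may be a stray phrase.** It occurs once, and the rest of the article reads as a trial looking for a difference. This is plausible. It does not remove the contradiction, but it bears on which repair comes first.

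**The size rests on assumptions.** The documents give no response rates and no margin. This is true, but the conclusion is the same at every rate and margin tried, and at 43 or 48 per arm.

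Two stronger readings are tempting, and the documents do not support them:

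- *That P > 0.05 will be reported as non-inferior.* No section says so. The text says only that P < 0.05 means a significant difference. The supportable statement is that no non-inferiority rule exists.
- *That intention-to-treat analysis itself bars a non-inferiority conclusion.* It does not. That it dilutes differences is a general tendency, not something shown for this trial. The planned set is also not pure intention-to-treat: section {20a} excludes subjects lacking main-result data, and section {20c} imputes nothing.

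**Conclusion.** The point holds. The design label contradicts the sample-size method and the planned test, and the missing margin is part of that contradiction, not detail left out of a condensed article. As written, no result of this trial could establish non-inferiority of antifungal response.

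The practical size is considerable. Under assumed control response rates of 30-50%, a regimen truly 15 points worse would escape detection in well over half of such trials. This rests on assumed rates, independent binomial outcomes and an uncorrected chi-square. The contradiction itself needs no assumption, because it can be read directly from the sections cited.

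**What to change.** **Preferred.** Delete the term from Trial design {8} and state the comparison as one of difference. In Statistical methods {20a}, add that the difference in response rate (experimental minus control) will be reported with its two-sided 95% confidence interval, and that P > 0.05 will not be read as equal or non-inferior efficacy. This changes wording only. The cost is that a non-inferiority claim is given up.

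**Alternative, if the sponsor keeps the label.** State and justify a margin for the primary response rate. This may be hard to do: on the comparator, the article says "Instruction of voriconazole shows no recommendation for patients with severe liver cirrhosis", and the same sentence extends this to liver failure. Replace the chi-square decision rule with the lower limit of the two-sided 95% interval against the margin, and add a per-protocol analysis as a supporting check. State the power at 96 patients openly: about 46-57% even for a 20-point margin, with 43 evaluable per arm and equal response rates of 25-50%. The cost is the margin justification, one further analysis set, and either a much larger trial or acceptance that a firm non-inferiority conclusion is unlikely.

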**Fig. 1 Fig1:**
[figure not shown]
Flow chart of this study

## Methods: participants, interventions, and outcomes

### Study setting {9}

The study will be conducted in the Department of Infectious Diseases, The Third Affiliated Hospital of Sun Yat-Sen University, a large Grade-A Tertiary Hospital in Guangzhou.

### Eligibility criteria {10}

#### Inclusion criteria

The following are the inclusion criteria:Patients 18–85 years of agePatients with the signing of informed consent and confirming enrollmentACLF was diagnosed according to guidelines for diagnosis and treatment of liver failure (2018) [13]: a presentation of extreme fatigue and severe gastrointestinal symptoms (anorexia, abdominal distension, nausea, and vomiting), progressive jaundice over a short period (total serum bilirubin ≥ 10 × ULN or a daily rise ≥ 17 μmol/L), a pronounced bleeding tendency (PTA ≤ 40% or INR ≥ 1.5), and any degree of potential complications (encephalopathy, clinical ascites, etc.) based on ongoing chronic liver diseasesIPA was diagnosed according to the latest EORTC/MGC consensus definition updated in 2020 [14, 15], including proven and probable IPAProven IPA: histopathologic examination of a pulmonary specimen obtained by needle aspiration or biopsy in which hyphae or melanized yeast-like forms are seen accompanied by evidence of associated tissue damage or recovery of the aspergillus by the culture of the alveolar lavage fluid obtained by a sterile fiberoptic bronchoscope lavage from a normally sterile and clinically or radiologically abnormal site consistent with an infectious disease processProbable IPA: host factors + clinical features (fever, cough, sputum, and other symptoms; signs such as rales in the lungs; pulmonary imaging in support of aspergillus infection) + mycological evidence

#### Exclusion criteria

The following are the exclusion criteria:Pregnant or lactating womenPatients with acute fatty liver in pregnancyPatients with HIV co-infectionPatients accompany with severe underlying diseasesHistory of allergic to voriconazole

#### Dropout criteria

The following are the dropout criteria:Patients with ALT or TBiL continuous elevation (more than 5 or 2 times higher than the baseline)Patients with central nervous system toxicity such as hallucinations and psychiatric abnormalities and plasma voriconazole trough concentration persistently exceeding 6 mg/L, which cannot be relieved by reducing the dose to 50 mg qdPatients who withdraw their consent during the study

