### Intervention description {11a}

Eligible patients will be randomized to either the experimental group or the control group. According to the recent research on related topics and the previous retrospective studies of our research group, the experimental group will receive the optimized voriconazole regimen: first loading dose, 6 mg per kilogram intravenously; second loading dose (twelve hours interval from first dose), 2 mg per kilogram intravenously; maintenance dose, 2 mg per kilogram intravenously twice daily.

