### Criteria for discontinuing or modifying allocated interventions {11b}

Persistent high trough concentrations are an independent risk factor for hepatic and central toxicity of voriconazole. Therefore, if ALT or TBiL is persistently elevated (i.e., a fivefold increase for ALT or a twofold increase for TBil above baseline) or central nervous system toxicity such as hallucinations and psychiatric abnormalities occur, and plasma voriconazole trough concentration persistently exceeding 6 mg/L, which cannot be relieved by reducing the dose to 50 mg qd, voriconazole can be discontinued and replaced with echinocandins for antifungal treatment or even withdrawn from the trial. A patient may also be withdrawn from the study for the following reasons: (1) lost to follow-up or (2) withdrawal of consent.

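### Toxicity is listed as a reason to drop out, so patients can leave because of an outcome event before CT response and week 4/8 mortality are known

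*Protocol article*

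**What the plan says.** The Dropout criteria, under Eligibility criteria {10}, have three entries:

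- "Patients with ALT or TBiL continuous elevation (more than 5 or 2 times higher than the baseline", with no further condition attached;
- CNS toxicity together with a trough persistently above 6 mg/L that is not relieved by cutting the dose to 50 mg once daily;
- withdrawal of consent.

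Section 11b covers the same toxicities with a graded, optional consequence: "voriconazole can be discontinued and replaced with echinocandins for antifungal treatment or even withdrawn from the trial". It continues, "A patient may also be withdrawn from the study for the following reasons", and names loss to follow-up and withdrawal of consent. The sentence adds these to the toxicity route, so toxicity is itself a stated way out of the study.

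The objective (section 7) is to "examine the efficacy and safety of voriconazole in the treatment of IPA in patients with liver failure". Adverse events and mortality at weeks 4 and 8 are secondary outcomes, section 22 names worsening liver function among the adverse events to monitor, and the primary response is judged partly on follow-up CT. Sections 18b and 20a promise an intention-to-treat analysis, and section 20c rules out imputation.

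**The concern.** Toxicity and liver deterioration are part of what the trial is meant to measure. If meeting a toxicity criterion ends participation, later CT scans, adverse events and vital status may go uncollected, and for a reason tied to prognosis. The patients who remain would be a selected group.

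The two sections also disagree on the consequence: one makes the event a dropout, while the other allows a switch of drug with trial withdrawal as a further option. They may differ on the trigger as well, because section 11b can be read as requiring the high trough and failed dose reduction for the liver criterion too. Two investigators following the same protocol could handle the same patient differently.

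Even if losses are equal in both arms, response can look too high and mortality too low in a trial intended as a dosing reference. If losses are unequal, the comparison between regimens is affected too.

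**Working it through.** **Plan's own figure.** Section 14 allows for 10% dropout: 43/(1 − 0.10) = 47.8, so 48 per arm and 96 in total. That step reproduces. It treats dropouts as not contributing to the analysis. (How the 43 was derived is a separate matter and is not used here.)

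**1. Can the disease alone meet the liver criterion?** The inclusion criteria require "progressive jaundice over a short period", met by bilirubin of at least 10 × ULN or a rise of at least 17 μmol/L a day. Assume a patient at 10 × ULN, a linear rise of 17 μmol/L a day, and ULN between 17 and 21 μmol/L. The criterion can mean 2 × or 3 × baseline.

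- To 2 × baseline: 10 × ULN/17 = 10.0 days (ULN 17) to 12.4 days (ULN 21).
- To 3 × baseline: 20 × ULN/17 = 20.0 to 24.7 days.

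Table 1 has post-baseline CT at weeks 2, 4, 6 and 8. Leaving on day 10–12 loses all four scans; leaving on day 20–25 loses three. Both mortality time points are lost either way if follow-up stops. A lower baseline at the same slope doubles sooner. A baseline of 20 × ULN takes 20 to 25 days to double. The elevation must also persist, which adds time.

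**2. How much of the response difference is left undetermined?** With m patients of unknown response in each arm of 48, the difference over all randomised patients can move by ±m/48. At 10% dropout, m ≈ 5 and 5/48 = 10.4 points. The standard error at an assumed 30% response in both arms is √(2 × 0.3 × 0.7/48) = 9.4 points.

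**3. Equal 10% dropout, complete cases analysed.** Let s be the response rate among dropouts and d their mortality.

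| Quantity | Formula | Result | Error |
|---|---|---|---|
| Response, s = 0 | 0.30/0.90 | 0.333 | +3.3 points |
| Response, s = 0.10 | (0.30 − 0.01)/0.90 | 0.322 | +2.2 points |
| Response, s = 0.30 | (0.30 − 0.03)/0.90 | 0.300 | 0 |
| Mortality, d = 1 | (0.735 − 0.10)/0.90 | 0.706 | −2.9 points |
| Mortality, d = 0.735 | (0.735 − 0.0735)/0.90 | 0.735 | 0 |

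The 73.5% is the lower end of the range section 6a gives where it describes IPA "with a significant increase in short-term mortality". The between-arm difference is unbiased when losses and the dropouts' outcomes are equal.

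**4. Unequal dropout.** Take 10 dropouts in total, none of whom responds, and a true response of 30% (14.4 of 48) in each arm.

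- 6 v 4: 14.4/42 = 0.343 and 14.4/44 = 0.327, a shift of 1.6 points.
- 7 v 3: 14.4/41 = 0.351 and 14.4/45 = 0.320, a shift of 3.1 points.

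Reversing the split reverses the sign.

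**5. Is imbalance likely?** Control follows the labelled Child–Pugh A/B regimen, in which "the loading dose remains unchanged and the maintenance dose is halved": 6 mg/kg twice, then 2 mg/kg twice daily. The experimental arm gets 6 mg/kg, then 2 mg/kg, then "maintenance dose, 2 mg per kilogram intravenously twice daily". Only the second loading dose differs. Section 14 assumes 60% v 30% with day-3 trough above 5 mg/L, which makes more triggers in control plausible. The documents do not say what fraction of those patients would go on to meet a dropout criterion, so no directional figure is offered.

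**The case against.** The strongest reply is that section 11b is the operative rule and already names stop-and-switch before withdrawal. The Dropout criteria state no follow-up consequence, and nowhere does the article say that visits or vital status stop after toxicity. Sections 18b and 20a point towards analysing everyone, and these are inpatients at one hospital. Continued follow-up may simply sit in the full protocol.

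Part of this stands. The triggering adverse event would be recorded, section 11b permits switching without withdrawal, and investigators may follow these patients anyway. But the point does not rest on silence: toxicity is listed as dropout alongside consent withdrawal, and section 11b itself counts withdrawal among its consequences. The intention-to-treat commitment in 18b applies to data that exist, and the follow-up sentence in 20a is a general statement of effort. An analysis plan cannot restore a scan or death date never obtained.

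Two further objections limit the size. If section 11b's trough condition applies to the liver criterion, bilirubin rising from liver disease alone triggers nothing. That reading removes the scenario in step 1, but it also shows that the two sections state different triggers. Second, the illustrations are selected. The ±10.4 points is an extreme bound, needing all the dropouts in one arm and none in the other to respond, and it treats the whole dropout allowance as missing. The 30% response has no source in the document and exceeds the 26.5% who survive if mortality is 73.5%. Using 26.5% instead, the standard error is √(2 × 0.265 × 0.735/48) = 9.0 points and the largest overstatement is 0.265/0.90 − 0.265 = 2.9 points, so little changes. The shifts of 1.6 to 3.1 points under unequal loss are about one-sixth to one-third of a standard error.

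**Conclusion.** The concern holds. As written, the protocol makes outcome events a route out of the trial, and its two sections conflict on the consequence. The resulting loss would be informative, and nothing in the stated analysis repairs it.

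The size is moderate and uncertain. At 10% dropout the data would leave a band of up to ±10.4 points around the response difference, slightly wider than one standard error. Under equal loss, the distortion within each arm is 0 to 3.3 points for response and 0 to 2.9 points for mortality. Bias between arms is zero if losses and dropouts' outcomes are alike. It is 1.6 to 3.1 points under the splits tried, with no established direction. These figures assume 30% response, 73.5% mortality, dropout at the planned 10%, and no outcome collection after departure. If investigators in fact follow these patients to week 8, the loss does not arise.

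**What to change.** Use one trigger wording in the Dropout criteria and section 11b, stating explicitly whether the trough and dose-reduction condition applies to the liver criterion; its clinical content is for the investigators. Label it as stopping or switching study drug. Let only withdrawal of consent or loss to follow-up end participation. State that every randomised patient, including those who stop or switch, stays on the Table 1 schedule for CT, adverse events and vital status to week 8 and is analysed as randomised. How a response after a switch to an echinocandin counts can be left to the SAP.

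The cost is a short amendment. The visits already exist in Table 1, so the added work is completing them for patients who stop the drug, about 10 of 96 at the planned dropout rate.
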